### Procedure

#### Phase I

During phase I, approximately 1400 eligible participants from across organisations will be invited to complete an online survey, of whom we aim 500 to complete the survey, to assess the following: (a) their interest in participating in a trial aiming to assess the use of sit-stand desks at work; (b) their preferences for different desk types (full desks vs desk mounts); and (c) their preference regarding the location (home vs workplace vs clinical research facility) for the baseline and follow-up assessments.

The survey will include a brief description of the trial and will ask people to indicate their willingness to participate, via a yes/no response. The proposed duration of the future full trial, the design of which this feasibility study aims to clarify, is 6 months, Due to resource restrictions, the duration of the randomised component of the proposed feasibility study will be 3 months. To gauge any potential differences in interest to participate as a function of the trial duration, all participants will be asked to respond to two relevant questions: one enquiring about their interest in a trial lasting 3 months and one enquiring about their interest in a trial lasting 6 months. The order in which these questions appear will be randomised. Participants will also be asked to indicate their preference regarding potential locations for the assessments to take place (home, workplace, or clinical research facility).

The survey will also include a brief description, with pictures, of the two different types of sit-stand desks available: full desks and desk mounts that are installed on top of existing desks. Links to videos demonstrating how each desk type works will also be provided.

The survey will also include questions relevant to participants’ demographic information, including age, gender, level of education, BMI, smoking status, salary band, and position within the organisation.

#### Phase II

Of the participants indicating an interest in taking part in the trial during phase I, 100 chosen at random will be visited by a researcher who will assess their workspaces for desk installation suitability. To do this, the researcher will measure the following: (a) the dimensions of the workspace, (b) the dimensions of existing desks, and (c) the dimensions of any available (empty) space. The researcher will also record (through photographs and notes) the configuration of the space (i.e. shape of the room) and of the furniture within that space, making note of any obstacles that might inhibit desk installation and/or use (e.g. shelves that would obstruct sit-stand desks being put into standing mode).

These measurements and records will be compared against measurements involving the space and room configurations needed to successfully install each desk type, identified from measuring acquired samples of each desk type.

#### Phase III

Twenty randomly selected participants of those whose workspaces will be measured during phase II will be randomised to either the use of sit-stand desks (full desks or desk mounts depending on their preference and workspace limitations) at work for 3 months or a waiting list control group. Those allocated to the waiting list control group will continue using their existing desks and will be offered sit-stand desks 3 months later.

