#### Exclusion criteria

Are already using sit-stand desksDo not have use of their own personal deskHave musculoskeletal disorders that make prolonged standing inadvisableHave chronic illnesses that prevent prolonged periods of standingAre planning to be absent from the workplace for more than 14 working days during the study periodAre pregnant

For phase I, 500 eligible employees will be targeted. Phase II will involve 100 participants. Both phases III and IV will involve 20 participants.

Eligible participants will be identified and recruited through (i) employment databases and invited via letter/email and (ii) adverts in local newsletters and flyers posted within the buildings of target organisations.

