#### Intervention

The intervention will comprise the provision of sit-stand desks at work for 3 months. Participants will be offered one of the two desk types according to their preferences and workspace restrictions: desk mounts or full desks. This is in line with the procedures adopted in previous studies [54, 69] and is expected to maximise the probability of desk use. Desk mounts involve a device that is installed on top of a conventional workplace desk often by means of a clamping arm. The device facilitates regular transitions between sitting and standing postures, predominantly while performing computer-based activities. It can be placed in standing mode via an easy upward pulling motion that lifts the display unit(s) and objects placed on the work surfaces. With full sit-stand desks, the entire surface area of the desk (and all items on it) can be adjusted to standing mode.

To enhance desk use, participants will also be given the following: (i) a demonstration of how their desk works, delivered in person by a researcher; (ii) written instructions on how to use the desks; (iii) information on the correct ergonomic posture; (iv) information on the benefits of standing, reducing sitting and breaking up sitting time; (v) guidance on gradually building up standing time; (vi) recommendations relating to the amount of time to increase standing and reduce sitting; and (vii) information on how the desks are used by others.

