#### Phase III

Practicalities of delivering the intervention, assessed by recording:° The time lapse between ordering the desks from the manufacturer and their delivery° Any permissions needed to install each desk type° The feasibility of training research staff to install desks° The feasibility of one person (a trained research assistant) installing each desk without help° The amount of time needed to install each desk° Any problems associated with delivering the desks to participants° Any problems installing each desk type° The practicalities associated with removing existing desks (applicable only when using full desks)
Circumstances and factors affecting desk use assessed via direct observations and diaries/logsProportion of participants dropping out between randomisation and the 3-month follow-upTrial-related outcomes, assessed at baseline (before randomisation) and at 3-month follow-up:° Physical activity energy expenditure estimated via Actiheart^3^ monitors° Sedentary behaviour measured using activPAL inclinometers^4^:Sitting time during (a) working hours (workplace sitting time) and (b) all waking hours (total sitting time)Sitting patterns (number of sit-to-stand transitions; sitting time accrued in prolonged bouts (≥30 min)) during (a) working hours (workplace sitting patterns) and (b) all waking hours (total sitting patterns)
° Cardio-metabolic related outcomes:BMI calculated from weight and heightWeight measured using a scaleHeight measured using a stadiometerFat mass and fat-free mass measured via a spectroscopy deviceBlood pressure, measured via an electronic monitorWaist-hip circumference measured using a tape measurePlasma total cholesterol, HDL, triglycerides and HbA1C, measured via non-fasting blood tests
° Musculoskeletal discomfort measured using the Nordic Musculoskeletal Questionnaire [80]° Ability to work, work productivity, presenteeism, absenteeism and job satisfaction measured using the Work ability index [81], the Stanford presenteeism scale [82] and Measure of job satisfaction [83]° Domain-specific sedentary behaviour measured using the SIT-Q-7d, a domain-specific last-7-day sedentary behaviour questionnaire [84]° Health symptoms, including neck pain, headache, back pain, fatigue, eye strain and loss of concentration, measured using a checklist° Health-related quality of life measured using the Euro-Quality of Life 5 (EQ-5D-5L) [85]° Food and drink consumption measured using a daily food log

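### Phase III draws its 20 participants at random without securing both desk types, although some of its delivery outcomes are defined by desk type; the risk is material only if one type is rare

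*Protocol article*

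**What the plan says.** Under Procedure, Phase II, of those who express interest in the survey, "100 chosen at random will be visited by a researcher who will assess their workspaces for desk installation suitability". Under Procedure, Phase III, the next step is "Twenty randomly selected participants of those whose workspaces will be measured during phase II will be randomised". The Exclusion criteria section confirms the number: "Both phases III and IV will involve 20 participants".

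Desk type is not set by design. Phase III gives it as "full desks or desk mounts depending on their preference and workspace limitations", and the Intervention section repeats this: "Participants will be offered one of the two desk types according to their preferences and workspace restrictions: desk mounts or full desks". The waiting list also receives the intervention in time, since those participants "will continue using their existing desks and will be offered sit-stand desks 3 months later".

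Under Outcomes and measures, Phase III, two delivery items are worded by desk type: the permissions needed, and "Any problems installing each desk type". A third, the practicalities of removing existing desks, is marked as applying only to full desks. One-person installation and installation time are worded for each desk, not for each desk type.

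**The concern.** The selection rule and these outcomes do not fit together well. The outcomes presuppose that both desk types are installed, but the rule leaves the number of each to chance. If few people would receive one of the types, a random 20 may contain one or none of them. If full desks are the rare type, the outcome on removing existing desks could end with no data at all.

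Phase II cannot fill the gap. The sample desks acquired there are measured to establish space requirements; the article does not say that they are installed at anyone's workplace.

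The information needed to avoid this is already in hand when the 20 are drawn: preference comes from the phase I survey and workspace fit from the phase II audit. The stated rule uses neither.

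**Working it through.** **Inputs**

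- Pool: 100 audited workspaces (Procedure, Phase II).
- Draw: 20, at random, with no minimum per desk type stated (Procedure, Phase III).
- Installations: up to 20, because the waiting list is offered desks after 3 months.
- K, the number among the 100 who would receive the less-used type: not in the document. The preference split is itself a phase I outcome. K is therefore an assumption, taken here from 5 to 30.
- Simplification: each of the 100 could be fitted with one type or the other.

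**The plan's own figures.** The article gives no figure for installations per desk type. Its only precision figures at n = 20 concern attrition. A Wilson interval with continuity correction reproduces them: 1.8 to 33.1% against the stated 2 to 33%, and 3.5 to 37.7% against the stated 3.5 to 38%. They do not bear on this point.

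**Formulas** (hypergeometric, 20 drawn from 100 without replacement)

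- P(0) = C(100 − K, 20) / C(100, 20)
- P(1) = P(0) × 20K / (81 − K)
- P(at most 1) = P(0) + P(1)
- Expected number = 20 × K / 100

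**Worked case, K = 5.** P(0) = (80 × 79 × 78 × 77 × 76) / (100 × 99 × 98 × 97 × 96) = 0.319. P(1) = 0.319 × 100 / 76 = 0.420. P(at most 1) = 0.739.

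**Worked case, K = 10.** P(0) = 0.095. P(1) = 0.095 × 200 / 71 = 0.268. P(at most 1) = 0.363.

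| K of 100 (assumed) | Expected among 20 | P(none) | P(at most one) |
|---|---|---|---|
| 5 | 1 | 32% | 74% |
| 10 | 2 | 10% | 36% |
| 15 | 3 | 3% | 15% |
| 20 | 4 | 0.7% | 5% |
| 30 | 6 | under 0.1% | 0.4% |

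**Sensitivity to dropout.** If the article's 10% attrition meant 18 desks instead of 20, binomial figures at a 10% share move from 12% (none) and 39% (at most one) to 15% and 45%. At a 20% share they move from 1% and 7% to 2% and 10%. The pattern is unchanged.

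**Could the pool supply a minimum?** With five per type as an illustration, the binomial chance that 100 audited people include at least five of the rarer type is 0.56 at a 5% share, 0.98 at 10% and above 0.999 at 20%. Where the pool can fill the minimum, the chance of selecting none or only one becomes zero.

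**The case against.** The strongest reply is that these outcomes are practical records, not estimates. One installation is enough to record permissions and problems; only the variation between installations is lost. Strictly, the items go unanswered only when there are none, and that chance is already down to 10% at K = 10 and 3% at K = 15. This stands. A reader might infer that delivery of the less-used type cannot be assessed at all, but that follows only with zero installations.

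Second, the split is unknown and the risk all but disappears for balanced splits. This also stands, and is why the table runs to K = 30. A type that few want would also be a small part of a main trial recruited in the same way, so thin data on it would cost less.

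Third, a reader might take the point further than the document allows:

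- *That a stated objective is defeated.* The delivery objective under Aim and objectives speaks of installing sit-stand desks without naming desk type. The objective that does name desk types concerns how many of each to obtain, and it rests on phase I and II data that this draw does not touch.
- *That only the immediate arm counts.* The waiting list is offered desks too, so the relevant number is up to 20.
- *That the same risk applies to the two organisations.* No phase III outcome is defined by organisation and no split between them is given.

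Finally, the article condenses a fuller protocol that might contain a quota. That is possible. But the comment concerns a selection rule that the article states, and as stated the rule is random with desk type left to follow.

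**Conclusion.** The point holds in a limited form. The stated draw does not secure installations of both desk types, while two phase III outcomes are worded for each type and one exists only for full desks. The chance of at most one installation of the less-used type is 15% at 15 of 100, 36% at 10 and 74% at 5. It falls to 5% at 20 and 0.4% at 30. The risk therefore deserves attention only if that type's share is about 15% or less, and the document does not say whether it is.

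These figures assume that all 20 receive a desk and that every audited workspace can take one type or the other. Nothing in the article is miscalculated on this point. It is a minor design improvement, worth making because it costs almost nothing.

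**What to change.** Amend the selection rule in Procedure, Phase III. Classify the audited participants by the desk type that would be installed, using phase I preference and phase II workspace fit. Then select the 20 at random within each type, with a small minimum per type where the pool allows. Five is an illustration; the investigators should set the number. State that desk-type proportions for the main trial come from phases I and II only. Allocation to desk or waiting list can stay as it is: strata by organisation, or randomisation within desk type by organisation, would be excessive for 20 people.

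The change takes a sentence or two and needs no extra participants or data. Its cost arises only if the minimum binds. The 20 then no longer mirror the natural desk-type mix, so the attrition and variability estimates become slightly less representative. Reporting the selection fractions makes this visible. For example, taking 5 of 10 of the rarer type and 15 of the other 90 gives fractions of 50% and 17%. The fix is weakest where the type is rarest, since at a 5% share the pool itself may hold fewer than five; hence the qualification about what the pool allows.

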#### Intervention

The intervention will comprise the provision of sit-stand desks at work for 3 months. Participants will be offered one of the two desk types according to their preferences and workspace restrictions: desk mounts or full desks. This is in line with the procedures adopted in previous studies [54, 69] and is expected to maximise the probability of desk use. Desk mounts involve a device that is installed on top of a conventional workplace desk often by means of a clamping arm. The device facilitates regular transitions between sitting and standing postures, predominantly while performing computer-based activities. It can be placed in standing mode via an easy upward pulling motion that lifts the display unit(s) and objects placed on the work surfaces. With full sit-stand desks, the entire surface area of the desk (and all items on it) can be adjusted to standing mode.

To enhance desk use, participants will also be given the following: (i) a demonstration of how their desk works, delivered in person by a researcher; (ii) written instructions on how to use the desks; (iii) information on the correct ergonomic posture; (iv) information on the benefits of standing, reducing sitting and breaking up sitting time; (v) guidance on gradually building up standing time; (vi) recommendations relating to the amount of time to increase standing and reduce sitting; and (vii) information on how the desks are used by others.

#### Randomisation

Following baseline assessments, participants will be randomised to the use of sit-stand desks at work or a waiting list control group, who will receive sit-stand desks 3 months later. The randomisation will be determined by a statistician independent from the research team, with the assistance of computer software.

#### Assessments

Of those randomised during phase II, 10 participants, five from the interventions group and five from the waiting list control group, will complete the baseline and follow-up assessments.

Based on their preference of location, participants will be visited by a researcher at their home, or place of work, or invited into a clinical research facility for all baseline assessments to be made prior to randomisation. The measurements will include anthropometric (height, weight, fat mass, fat-free mass, waist and hip circumference) and blood pressure measurements and collection of a blood sample to measure total cholesterol, HDL, triglycerides and HbA1C. Participants will also be asked to complete a questionnaire to assess musculoskeletal discomfort and other health symptoms, ability to work, presenteeism, absenteeism and job satisfaction, quality of life and domain-specific sedentary behaviour.

They will also be fitted with a combined heart rate and movement sensor (Actiheart) on the chest and asked to complete either a stepping test, if assessed at home or work, or a treadmill test if assessed in the clinical research facility. They will also be fitted with a thigh-based accelerometer (activPAL) to measure baseline sitting standing and stepping time and sitting and standing patterns. Both devices will be worn for 24 h/day for seven consecutive days. Participants will also be required to complete a brief daily log with wake and sleep times, work hours and any device removal, as well as their food intake. Participants will receive instructions on devices and log use. Devices and logs will be collected by research staff at the end of the 7-day period.

Follow-up assessments will occur 3 months after baseline. One week prior to this, participants will be visited by a research assistant who will fit them with the inclinometers and monitors, to be worn 24 h/day for seven consecutive days. Data from these will be used to assess the impact of the intervention on sitting and standing time, as well as sitting and standing patterns, and physical activity energy expenditure. Participants will also be asked to complete the daily logs. Seven days later, depending on participants’ location of preference, devices and logs will either be collected by research staff, who will visit participants at home or at work, or will be returned by participants visiting the clinical research facility. At the same time, participants will provide a blood sample and have their anthropometric and blood pressure measurements taken. They will also be asked to complete the same questionnaires previously completed at baseline.

After the follow-up assessments, participants will receive a personalised report with feedback on their health status, levels of physical activity, fitness and sedentary behaviour and information on how these have changed over time. If any of the assessments indicate abnormalities, participants will be notified of their results by the study clinician ([name]) in the first instance and then instructed to visit their general practitioner.

During phase III, all participants given sit-stand desks will be asked to complete short weekly video and/or paper-based diaries to record the circumstances under which they choose to use the desks to stand, as well as the barriers and facilitators to standing. At random times, participants will also be directly observed in their workplaces by a researcher to record their behaviour, including the different tasks undertaken while standing vs sitting. The content of the diaries and the results from the observations will be analysed to create a list of the possible factors that facilitate and inhibit desk use. This information will be used in designing the main trial to maximise the possibility of desk use.

#### Phase IV

Participants offered sit-stand desks will be interviewed about their experiences of using sit-stand desks, in order to explore the circumstances under which they chose to stand both at work and in other contexts; their attitudes towards standing in a predominantly sitting environment, i.e. the workplace; and the acceptability of the intervention and of the study procedures. Employer representatives will also be interviewed, in order to explore the acceptability of sit-stand desks at the organisational level. Interviews will be semi-structured and will last approximately 30 min. An interview schedule will be designed based on the existing literature and in collaboration with an expert qualitative researcher with experience in research within the field of physical activity and public health. The interview schedule will be pre-piloted on a small number of employees within the target organisation who currently use sit-stand desks.

### Outcomes and measures

#### Phase I

The following outcomes will be assessed via an online questionnaire:Proportion of eligible participants interested in taking part in a 3-month trial on the use of sit-stand desks at workProportion of eligible participants interested in taking part in a 6-month trial on the use of sit-stand desks at workDemographic characteristics° Age° Gender° BMI° Smoking status° Salary band° Highest educational qualification° Position within company
Proportion of participants preferring desk mounts vs full desksProportion of participants preferring to be assessed at home vs work vs the clinical research facility

#### Phase II

Proportion of workplaces suitable for use of full desks and desk mounts assessed via workplace auditing and recordingProportion of workspaces permitting participants’ choice of desk to be installed

#### Phase III

Practicalities of delivering the intervention, assessed by recording:° The time lapse between ordering the desks from the manufacturer and their delivery° Any permissions needed to install each desk type° The feasibility of training research staff to install desks° The feasibility of one person (a trained research assistant) installing each desk without help° The amount of time needed to install each desk° Any problems associated with delivering the desks to participants° Any problems installing each desk type° The practicalities associated with removing existing desks (applicable only when using full desks)
Circumstances and factors affecting desk use assessed via direct observations and diaries/logsProportion of participants dropping out between randomisation and the 3-month follow-upTrial-related outcomes, assessed at baseline (before randomisation) and at 3-month follow-up:° Physical activity energy expenditure estimated via Actiheart^3^ monitors° Sedentary behaviour measured using activPAL inclinometers^4^:Sitting time during (a) working hours (workplace sitting time) and (b) all waking hours (total sitting time)Sitting patterns (number of sit-to-stand transitions; sitting time accrued in prolonged bouts (≥30 min)) during (a) working hours (workplace sitting patterns) and (b) all waking hours (total sitting patterns)
° Cardio-metabolic related outcomes:BMI calculated from weight and heightWeight measured using a scaleHeight measured using a stadiometerFat mass and fat-free mass measured via a spectroscopy deviceBlood pressure, measured via an electronic monitorWaist-hip circumference measured using a tape measurePlasma total cholesterol, HDL, triglycerides and HbA1C, measured via non-fasting blood tests
° Musculoskeletal discomfort measured using the Nordic Musculoskeletal Questionnaire [80]° Ability to work, work productivity, presenteeism, absenteeism and job satisfaction measured using the Work ability index [81], the Stanford presenteeism scale [82] and Measure of job satisfaction [83]° Domain-specific sedentary behaviour measured using the SIT-Q-7d, a domain-specific last-7-day sedentary behaviour questionnaire [84]° Health symptoms, including neck pain, headache, back pain, fatigue, eye strain and loss of concentration, measured using a checklist° Health-related quality of life measured using the Euro-Quality of Life 5 (EQ-5D-5L) [85]° Food and drink consumption measured using a daily food log

